#### Analysis populations

Efficacy, safety, and general characteristics data will be analyzed for all randomized patients. Primary efficacy analysis will also be conducted on the per-protocol (PP) population. The primary endpoint will analyze all randomized patients (on an intent-to-treat (ITT) basis) and per-protocol (PP) population.

The ITT population is defined as all randomized patients. The PP population is defined as all randomized patients without major protocol violations.

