### Study drug administration

Group 1 receives an intramuscular single dose of Naldebain^®^ 24 ± 12 h prior to surgery. The suggested injection site is the musculature of the buttocks. Care is taken to ensure that the drug is not injected into the adipose tissue. Group 2 receives intravenous PCA with fentanyl through 48 h postsurgery.

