##### Study day 1 (all eligible patients)

Eligible patients are required to check into the clinical site before surgery (day 0). The following procedures are performed at check-in: 1) review inclusion/exclusion criteria; 2) randomization; 3) review of concomitant medications; and 4) review of adverse events (AEs).

Additional laboratory tests are requested as required by the investigator.

All eligible patients are hospitalized and randomized into the two treatment groups: Group 1—intramuscular Naldebain^®^ (150 mg nalbuphine sebacate) 24 ± 12 h before surgery; Group 2—Intravenous PCA with fentanyl through 48 h postsurgery.

For pain assessment, patients in Groups 1 and 2 rate their pain intensity using the VAS pain scale prior to dosing or at day 1, respectively.

Vital signs are checked prior to dosing and once daily until day 6.

Group 1 receives Naldebain^®^, and the injection site is evaluated within 1 h prior to dosing.

##### Study day 0 to 5

All patients are given general anesthesia prior to their scheduled surgical procedure. If patients require additional medication for the treatment of pain, ketorolac and morphine can be used as supplemental analgesics as required. Post-surgery, the following evaluations are performed: 1) for pain assessment, all patients rate their average pain intensity using a VAS pain scale (assessments are performed before the first use of PCA or supplemental analgesics and then at 4 ± 1, 24 ± 2, 32 ± 3, and 48 ± 4 h, and once daily on day 3 to day 5 following surgery); 2) BPI evaluation is performed on day 2; 3) vital signs (temperature, respiratory rate, blood pressure, and heart rate) are examined once daily prior to the final visit; 4) in Group 1 (the IM-Naldebain^®^ group), the injection site is evaluated once daily until the final visit; 5) a review of concomitant medication and adverse events are record; and 6) in Group 2 (the IV-PCA group), the amount of fentanyl used is recorded from day 0 through day 2.

##### Study day 6

The following evaluations are performed at day 6: 1) for pain assessment, patients rate their pain intensity in the patient diary; 2) BPI is evaluated; 3) vital signs (temperature, respiratory rate, blood pressure and heart rate) are examined; 4) the injection site is evaluated; 5) a review of the AE record; and 6) a review of concomitant medication.

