#### Adverse event reporting

All AEs, regardless of causality, that occur between the time the study medication is administered and completion of the treatment phase are reported. Those meeting the definition of SAEs are reported using the SAE form.

All AEs, regardless of seriousness, severity, or presumed relationship to the study drug, are recorded using medical terminology in the source document and the CRF. Whenever possible, diagnoses are given when signs and symptoms are due to a common etiology (e.g., cough, runny nose, sneezing, sore throat, and head congestion should be reported as “upper respiratory infection”). Investigators must record in the CRF their opinion concerning the relationship of the AE to study therapy. All measures required for AE management must be recorded in the source document and according to sponsor instructions.

The investigator must report all such events to the appropriate independent ethics committee (IEC)/institution review board (IRB) that approved the protocol unless otherwise required and documented by the IEC/IRB.

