#### Safety analysis

For the safety analysis, continuous variables will be tested using a *t* test and categorical variables will be compared by chi-square or Fisher’s exact test. The coding system used will be the Medical Dictionary for Regulatory Activities (MedDRA).

AEs will be summarized descriptively according to body system, MedDRA preferred term, center, treatment, and overall outcome. If more than one type of event occurs within a system organ class/preferred term for the subject, the subject is counted only once when summarizing the data by system organ class/preferred term. Incidence tables of intensity, drug relationship, drug-related AE (including certain, probable, and possible), action taken regarding the study drug, and whether treatment was required for an event or SAE will be presented by center, treatment, and overall outcome. Incidence rates ≧2%, ≧10%, and rates for Naldebain^®^ greater than two times PCA fentanyl will be presented.

In terms of severity and relationship summaries, the most severe event and the most directly related event will be presented in summary tables in the case of multiple occurrences per subject. Only treatment-emergent events will be included in the AE summary; other events will only be listed. Treatment-emergent events include events that start on or after the first day of study drug administration, that were not present at baseline, or were present at baseline but increased in severity after the start of study drug administration.

A frequency table of injection site will be presented according to center, time, and treatment. Descriptive statistics of recovery duration (hours, defined as from first score 0 over second score 0 or 1) for injection site assessment will be presented according to center and treatment.

Incidence of SAEs will be tabulated. SAE incidents will be summarized descriptively according to center, system organ class, preferred term, treatment group, and overall outcome.

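### Safety is summarized over all randomized patients although only treatment-emergent events are counted, so any patient never given study drug dilutes that arm's TEAE rate

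*Protocol article*

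**What the plan says.** **Population.** The Analysis populations section assigns safety data to everyone randomized: "Efficacy, safety, and general characteristics data will be analyzed for all randomized patients". Two sets are defined. For the first, "The ITT population is defined as all randomized patients"; the second is the per-protocol set. No set of treated patients appears in the article, and nothing says whether safety is grouped by assigned or by received treatment.

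**Events counted.** Incidence of TEAE is a named safety endpoint (Study endpoints). The Safety analysis section states: "Only treatment-emergent events will be included in the AE summary; other events will only be listed". It anchors the definition to dosing: "Treatment-emergent events include events that start on or after the first day of study drug administration". The Adverse event reporting section uses a similar window, for AEs "that occur between the time the study medication is administered and completion of the treatment phase are reported".

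**Timing.** Table 1 places randomization on day −1. Under Study drug administration, "Group 1 receives an intramuscular single dose of Naldebain^®^ 24 ± 12 h prior to surgery". PCA fentanyl comes later: the section on study days 0 to 5 places its first use after surgery and records fentanyl use from day 0 through day 2.

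**Listings.** AE incidence is to be shown at thresholds of 2% and 10%, and "rates for Naldebain^®^ greater than two times PCA fentanyl will be presented".

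**The concern.** The numerator of the TEAE rate depends on having received study drug, while the denominator depends only on having been randomized. A patient who is randomized and then leaves before dosing is counted as event-free in the AE summary, whatever happens to that patient. This lowers the absolute rate in the affected arm.

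The two arms are not equally exposed to the problem. If surgery is cancelled or a patient withdraws between the Naldebain injection and the end of surgery, a Naldebain patient has already been dosed but a PCA patient has not. Undosed patients are therefore more likely in the PCA arm. The PCA rates would then be diluted more than the Naldebain rates, and both the comparison and the two-fold listing would shift.

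Safety is part of the primary objective (Objectives section), so the denominator matters.

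**Working it through.** **Inputs.** 110 randomized 1:1 (Overall design), so 55 per arm. Margin 10, SD 18, 80% power, one-sided 97.5% interval, 104 patients, 5% predicted dropout (Number of patients and randomization). The number randomized but never dosed, u, is not given and is an assumption here.

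**The plan's own figures.** With a true difference of zero, the normal approximation gives 51 per arm (102 in total). The noncentral t calculation gives 52 per arm (104 in total) with power 0.801, which matches. Dropout: 104/0.95 = 109.5, rounded up to 110, which also matches. The planned losses are 110 − 104 = 6.

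**Dilution formula.** Reported rate = true rate among treated × (55 − u)/55. One undosed patient lowers the rate by a relative 1/55 = 1.8%, three by 3/55 = 5.5%, and six by 6/55 = 10.9%.

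Reported rate in one arm, with the shortfall in percentage points in brackets:

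| u in the arm | (55 − u)/55 | True 30% | True 50% | True 70% |
|---|---|---|---|---|
| 0 | 1.000 | 30.0% (0) | 50.0% (0) | 70.0% (0) |
| 1 | 0.982 | 29.5% (0.5) | 49.1% (0.9) | 68.7% (1.3) |
| 3 | 0.945 | 28.4% (1.6) | 47.3% (2.7) | 66.2% (3.8) |
| 6 | 0.891 | 26.7% (3.3) | 44.5% (5.5) | 62.4% (7.6) |

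The row u = 6 supposes that all planned losses are undosed and fall in a single arm.

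**Effect on the comparison.** If the true rates are equal and only the PCA arm has undosed patients, the apparent Naldebain/PCA ratio is 55/(55 − u): 1.02 for u = 1, 1.06 for u = 3 and 1.12 for u = 6. For an event to be listed wrongly as more than twice PCA, the true ratio must already exceed 2 × 52/55 = 1.89 (u = 3) or 2 × 49/55 = 1.78 (u = 6).

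**Effect on the listings.**
- Five PCA patients with an event are 5/55 = 9.1%, below the 10% threshold, but 5/49 = 10.2% of those treated when u = 6.
- One patient is 1/55 = 1.8%, below the 2% threshold, but 1/49 = 2.04% when u = 6.
- With 11/55 = 20% on Naldebain and five PCA patients affected, the ratio is 20/9.1 = 2.2 on 55 and 20/10.2 = 1.96 on 49. The event would be listed only because of the denominator. In this example the change needs u of at least 5, since at u = 5 the ratio is 20/10 = 2.0, which is not greater than two.

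**The case against.** **The effect may be nil, and its size is assumed.** This stands. The 5% is a predicted dropout rate, and the article does not say that dropouts are undosed; patients can also withdraw after dosing. Patients are in hospital from randomization and surgery follows about a day later, so the interval for loss is short. Dropouts and withdrawals will be summarized by treatment group, so a reader could see some of the losses. Six undosed patients in one arm is an extreme case.

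**A condensed article leaves population details to the full protocol or SAP.** This holds for a grouping rule, whose absence alone would not be a finding. It does not hold for the denominator, because the article states which patients enter the safety analysis. If an unseen SAP names a treated set, this sentence contradicts it.

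**Stronger readings that the article does not support.**
- A reader might infer that AEs are collected only after study drug. Table 1 has an AE record from day −1 without restricting it to one arm, the check-in procedures include AE review for all eligible patients, and events that are not treatment-emergent are listed. The problem lies in what is counted, not in what is recorded.
- A reader might infer that safety is to be analyzed by assigned treatment, so that events in switched patients are credited to the wrong drug. The intent-to-treat wording is attached to the primary endpoint only, and no grouping rule is stated for safety.
- A reader might infer that the rule favors Naldebain. If undosed patients are mainly in the PCA arm, it is PCA that looks safer, and the listing would flag too many Naldebain events.

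**A treated set has its own asymmetry.** This also stands. A Naldebain patient qualifies before surgery and a PCA patient only afterwards. After a cancelled operation, the first could be in the set and the second out of it. This is the reason to keep the all-randomized table as well.

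**Conclusion.** The point holds as a mismatch between a stated denominator and a stated counting rule. A randomized patient who is never dosed is counted as event-free in the TEAE summary, and each one lowers that arm's rate by a relative 1.8%.

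Under the assumption of 0 to 6 undosed patients in one arm and true rates of 30% to 70%, the shortfall runs from nil to 7.6 percentage points. If everyone is dosed there is no effect. With one undosed patient it is about 0.5 to 1.3 points.

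That the PCA arm is the more exposed follows from the order of randomization, injection, surgery and PCA; the article gives no count to confirm it. The direction would then be against Naldebain. The efficacy analyses are not touched. The likely effect is small, but the article's own listings use fixed thresholds that a few patients can cross, and the change is cheap, so it should be made.

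**What to change.** In the Analysis populations section, take safety out of the all-randomized sentence and add: *Safety will be analyzed in all randomized patients who received Naldebain or started PCA fentanyl, grouped by the treatment received.* Keep ITT and per-protocol for efficacy. Present the all-randomized safety table as supportive, and report how many patients in each arm were randomized but not dosed.

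The cost is one sentence, one population flag and one extra table. No visit, data item or sample size changes. The downside is a small departure from the randomized comparison, and it can differ by arm because PCA patients qualify only after surgery. The supportive table shows whether this matters.

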#### Hypotheses and level of significance

Statistical analyses will be performed on the data to compare the Naldebain^®^ group with the PCA group. All statistical tests will be two-sided and evaluated at a level of significance of 0.05.

#### Dropouts, premature termination, and missing values

The dropouts, premature termination of study medication, and withdrawal will be summarized and analyzed according to treatment groups. A last observation carried forward procedure will be used to estimate the missing data for efficacy variables.

#### Baseline demographics

Descriptive statistics for demographic and background information are obtained for both groups at the screening visit.

#### Safety analysis

For the safety analysis, continuous variables will be tested using a *t* test and categorical variables will be compared by chi-square or Fisher’s exact test. The coding system used will be the Medical Dictionary for Regulatory Activities (MedDRA).

AEs will be summarized descriptively according to body system, MedDRA preferred term, center, treatment, and overall outcome. If more than one type of event occurs within a system organ class/preferred term for the subject, the subject is counted only once when summarizing the data by system organ class/preferred term. Incidence tables of intensity, drug relationship, drug-related AE (including certain, probable, and possible), action taken regarding the study drug, and whether treatment was required for an event or SAE will be presented by center, treatment, and overall outcome. Incidence rates ≧2%, ≧10%, and rates for Naldebain^®^ greater than two times PCA fentanyl will be presented.

In terms of severity and relationship summaries, the most severe event and the most directly related event will be presented in summary tables in the case of multiple occurrences per subject. Only treatment-emergent events will be included in the AE summary; other events will only be listed. Treatment-emergent events include events that start on or after the first day of study drug administration, that were not present at baseline, or were present at baseline but increased in severity after the start of study drug administration.

A frequency table of injection site will be presented according to center, time, and treatment. Descriptive statistics of recovery duration (hours, defined as from first score 0 over second score 0 or 1) for injection site assessment will be presented according to center and treatment.

Incidence of SAEs will be tabulated. SAE incidents will be summarized descriptively according to center, system organ class, preferred term, treatment group, and overall outcome.

For laboratory data, descriptive statistics of hematology, biochemistry, and urinalysis data will be presented according to parameter, center, visit, treatment, and overall data. Net changes from baseline (treatment–baseline) of hematology, biochemistry, and urinalysis results will be compared between treatments using analysis of variation (ANOVA) with baseline as the covariate. The baseline for laboratory data will be defined as the screening visit. If no data exist for the screening visit, the baseline will be defined as day 0.

For vital signs, descriptive statistics of vital signs including systolic and diastolic blood pressure, heart rate, respiratory rate, and body temperature will be presented according to center, visit, treatment, and overall outcome. Net change of vital signs compared with baseline (treatment–baseline) will be analyzed between treatments using ANOVA with baseline as the covariate. A frequency table of physical examinations with abnormal results will also be presented according to center, treatment, and overall outcome.

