## Methods and design

### Overall design

A randomized, positive-controlled, single-dose, parallel-design study will be conducted with 110 male and female patients scheduled to undergo elective laparotomy to assess the safety and efficacy of an intramuscular injection of Naldebain^®^. The study was designed to include a 5% dropout rate as taken from a previous published work [8].

A total of 110 eligible hospitalized patients will be randomized into one of two treatment groups in a 1:1 ratio. Group 1 is the intramuscular Naldebain^®^ (IM-Naldebain^®^ group) and Group 2 is the intravenous PCA with fentanyl (IV-PCA group). Group 1 receives a single dose of Naldebain^®^ (150 mg nalbuphine sebacate) intramuscularly 24 ± 12 h before surgery. Group 2 receives intravenous PCA with fentanyl through 48 h postsurgery. If PCA with fentanyl is deemed unnecessary by both investigator and patient, the PCA machine can be removed prior to the completion of 48 h as required. If patients require additional medication for treatment of pain, ketorolac and morphine can be used as supplemental analgesics as required. Both groups will undergo follow-up observation until the final visit (from the day of discharge through day 6–30). Statistical analyses will be performed on the data to compare the two groups.

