##### Final visit (discharge, day 6–30)

For safety concerns, the study will follow-up each patient until discharge (within a time window for discharge of 6–30 days). The patients will be evaluated for: 1) vital sign (temperature, respiratory rate, blood pressure, and heart rate) examination; 2) injection site evaluation; 3) laboratory tests, including hematological and biochemical tests, and urinalysis; 4) patient satisfaction (at the final visit, each patient is asked the following question (Table 2): “How satisfied were you with your postsurgical analgesia?” and patients are asked to classify themselves as either “highly satisfied,” “satisfied,” “uncertain,” “dissatisfied,” or “very dissatisfied”); 5) physical examination; 6) review of the AE record; and 7) review of concomitant medication.

**Table 2 Tab2:** Five-point rating of patient satisfaction

Rating	Description
1	Highly satisfied
2	Satisfied
3	Uncertain
4	Dissatisfied
5	Very dissatisfied

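### Treatment-emergent events are counted from first study drug, so preoperative events count in the Naldebain arm but not in the PCA arm

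*Protocol article*

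**What the plan says.** All references are to the protocol article.

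- **Summary rule (Safety analysis).** "Treatment-emergent events include events that start on or after the first day of study drug administration", provided they were absent at baseline or worsened after drug start. The same section adds: "Only treatment-emergent events will be included in the AE summary; other events will only be listed".
- **Naldebain timing (Overall design; Study drug administration).** One intramuscular injection, 24 ± 12 h before the operation. Table 1 places it on day −1.
- **PCA timing.** Overall design says "Group 2 receives intravenous PCA with fentanyl through 48 h postsurgery" and gives no clock time for the start. Under Study day 0 to 5, the postoperative pain ratings are scheduled so that "assessments are performed before the first use of PCA or supplemental analgesics and then at 4 ± 1, 24 ± 2, 32 ± 3, and 48" h, and in the PCA arm "the amount of fentanyl used is recorded from day 0 through day 2".
- **Reporting rule (Adverse event reporting).** All adverse events "that occur between the time the study medication is administered and completion of the treatment phase are reported". The treatment phase is not defined.
- **Schedule (Table 1; Final visit).** Adverse events are recorded from day −1 to discharge with no arm-specific footnote, although the table footnotes other rows by arm. On the end of observation: "the study will follow-up each patient until discharge (within a time window for discharge of 6–30 days").
- **Use of the result.** Incidence of treatment-emergent events is the first safety endpoint, and safety is part of the primary objective. Safety analysis names chi-square or Fisher's exact test for categorical safety variables and plans a display of rates more than twice as high under Naldebain as under PCA.

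**The concern.** Counting from first study drug gives comparable windows when both arms start drug at the same point in the patient's course. Here one arm starts before the operation and the other after it. Nausea or headache on day −1 is treatment-emergent in a Naldebain patient and only a listing entry in a PCA patient. If it persists in the PCA patient, it is present at baseline and counts only if it worsens.

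At stake is the first safety endpoint. Two arms with identical event rates over the same calendar period could show different incidences because of the counting rule alone. The two-times display is the most exposed, since for rare terms a few events counted in one arm only can move a ratio a long way. Without the comparator's events from the same hours, preoperative drug effects of Naldebain also cannot be separated from background.

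**Working it through.** **1. When each window opens.**

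- Naldebain: 24 − 12 = 12 h and 24 + 12 = 36 h before surgery.
- PCA: day 0. This is inferred, but firmly: the first postoperative pain rating precedes first PCA use, and fentanyl is accounted for on days 0 to 2 only.

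**2. Length of the difference.** Taking surgery as time zero and the same end of follow-up in both arms, relative excess = extra hours / hours after surgery.

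| End of follow-up | Hours after surgery | 12 h extra | 24 h extra | 36 h extra |
|---|---|---|---|---|
| Day 6 | 6 × 24 = 144 | 12/144 = 8.3% | 24/144 = 16.7% | 36/144 = 25.0% |
| Day 30 | 30 × 24 = 720 | 12/720 = 1.7% | 24/720 = 3.3% | 36/720 = 5.0% |

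Read by whole calendar days, Table 1 puts the two openings one day apart (day −1 against day 0), which lies inside the 12 to 36 h range.

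**3. How the difference could act on incidence.** Let p be the proportion with an event in the shared window, and q the proportion with an event in the extra preoperative period. Assume both are equal in the two arms and independent. Then the PCA arm shows p and the Naldebain arm shows 1 − (1 − p)(1 − q), an excess of q(1 − p). The article gives neither p nor q, so the following values are assumptions that show the mechanism and are not estimates:

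- q = 0: no difference, whatever p is.
- p = 0.10, q = 0.02: 1 − 0.90 × 0.98 = 11.8% against 10%, ratio 1.18.
- p = 0.10, q = 0.10: 1 − 0.90 × 0.90 = 19.0% against 10%, ratio 1.9.
- p = 0.02, q = 0.05: 1 − 0.98 × 0.95 = 6.9% against 2%, ratio about 3.4, past the two-times threshold with no true difference.

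**4. The other rules side by side.**

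- *Opening.* Safety analysis works by the day of first administration; Adverse event reporting works by the time of administration. For Naldebain, both include the operation. For PCA, the day reading can include anaesthesia and surgery on day 0, and the time reading excludes them.
- *Who can have an event.* The Adverse events section defines an event in a patient who has been given study drug. Taken literally, a PCA patient has none on day −1, yet Table 1 schedules the record from day −1 and the check-in procedures for all eligible patients include an adverse event review.
- *Closing.* The reporting rule ends with an undefined treatment phase; Table 1 ends at discharge.

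**The case against.** The strongest case on the other side is that counting from first drug is a conventional definition, that adverse events are said to be summarized descriptively, and that an additional common-window table is ordinary analysis-plan detail. No safety margin or safety power is claimed. The only events whose status would change are those of PCA patients before day 0, who have had neither study drug nor surgery, so their number may be small. Preoperative events under Naldebain may be genuine drug effects. Any bias runs against the investigational product, so it cannot make Naldebain look falsely safe.

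Most of this stands and limits the weight of the point. It does not remove it: the article already fixes the rule, and following it as written produces unequal windows. The use of a formal test on event incidence is itself an inference from a general sentence about categorical safety variables; the two-times display is explicit.

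Three stronger readings are tempting and not supported:

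- *That PCA events during anaesthesia and surgery are excluded from the summary.* The summary rule works by day, and both surgery and first PCA use fall on day 0. Exclusion follows only from the reporting rule, so this is an ambiguity.
- *That PCA reporting stops at 48 h or at removal of the device.* Nothing equates the treatment phase with the PCA period. Study duration gives one treatment and observation period of about 8 days, which matches day −1 through day 6 counted inclusively (6 + 1 + 1 = 8), and Overall design follows both arms to the final visit.
- *That the inflation of incidence can be stated as a percentage.* That would need a base rate and a hazard that is the same before surgery as after laparotomy; the article supports neither.

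**Conclusion.** The point holds for the preoperative period. As written, the summary rule counts events over an extra 12 to 36 h in the Naldebain arm, and the direction of any bias in crude incidence is against Naldebain. The size in time depends on discharge: 8% to 25% at day 6, about 2% to 5% at day 30. The size in incidence is unknown and could be nil. The conclusion assumes that PCA is first used after surgery, which the article implies clearly without giving a start time.

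Separately, the day and time wordings leave the status of PCA-arm events during the operation open, and the end of reporting is undefined and does not match Table 1. The safety comparison is affected; the primary efficacy endpoint and the sample size are not.

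**What to change.** 1. For the between-arm comparison, including the two-times display, count new or worsened adverse events in both arms from randomization (day −1) through day 6. Write the anchor as randomization itself, because an injection 36 h ahead may fall before the calendar day preceding surgery. Day 6 is the earliest discharge in Table 1, so a fixed end there does not depend on length of stay, which is itself an endpoint.
2. Add a postoperative-only table from surgery to day 6, and keep a summary to the final visit, noting that its length varies with discharge (day 6 to 30).
3. Keep the drug-start definition as a supplementary summary, so that preoperative events under Naldebain stay visible.
4. Align the Adverse events, Adverse event reporting and Safety analysis sections with Table 1: one opening and one closing point for both arms, and a definition of the treatment phase or its removal.

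The cost is a wording change and one or two extra tables. Table 1 already schedules the record in both arms from day −1. Before relying on it, confirm that sites recorded day −1 events in PCA patients, since the reporting section taken literally did not ask for them. No treatment or clinical procedure changes.
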